### Monitoring and audit

In this trial, monitoring will be conducted by Mirai Iryo Research, Inc. and the monitoring staff of the lead facility. Biannual routine monitoring sessions will be performed based on the monitoring reports prepared by the Research Administration Office. These sessions involve a comprehensive meeting with all or some representatives of group leaders, principal researchers, administrative offices, the Efficacy and Safety Evaluation Committee, and participating institutions. Interim analysis was not planned for this study because the follow-up period for the primary analysis is short, and any safety issues with the participants could be ascertained through periodic monitoring. Routine on-site monitoring will occur at least once every 3 months to review study progress and protocol compliance, with additional visits triggered by SAEs, major protocol deviations, or other emerging issues. Key source-data verification will include informed consent, eligibility, primary and secondary endpoints, SAEs, and protocol compliance. Adherence—including the scheduled start time, infusion rate, and duration of each dose—will be verified during these visits and during independent audits (Supplementary data 1, 2, and 3). A risk-based sampling strategy will be applied, with 100% verification of informed consent and SAEs and random sampling for efficacy endpoints.

The Clinical Research Support Unit of the Japanese Society for Regenerative Medicine (CRS JSRM) will provide education and conduct audits aimed at improving the scientific and ethical quality of research. Auditors will visit the representative facilities of the trial to verify the facility’s Institutional Review Board (IRB) documents and patient consent forms and reconcile the data on forms submitted to the office with medical records, following the audit plan developed by the CRS JSRM Unit. Auditing is scheduled to take place three times: October 24, 2024; June 17, 2025; and April 2026. On-site, document, and operational audits will be conducted to ensure data integrity, compliance with Standard Operating Procedures, and proper trial management. The audit is independent of the sponsor and investigators.

### Confidentiality

A designated party is responsible for storing all study-related information and materials; this responsibility includes the retention of records relevant to the study (copies of application documents, notification documents from the director, various application forms and reports, study-related materials, and other documents or records necessary to ensure data reliability). Furthermore, personal information will be protected during the disposal of documents or materials by shredding and incinerating physical documents (for electronic data, this involves using dedicated data deletion software or physical destruction to render the data irrecoverable). The principal investigator will take measures to ensure that these documents are not accidentally or prematurely destroyed.

Retention period: Documents will be retained for 10 years after the study’s end is reported or for 8 years after the final results are published, whichever period is longer.

## Discussion

This trial assesses whether short-course antibiotic therapy of 24–72 h for AC with appropriate biliary drainage is non-inferior to standard-course therapy of 96–168 h. A retrospective cohort study indicated comparable effectiveness between short-course and standard-course therapy for AC, with complications appearing to be more frequent with standard-course therapy (14–16,49). Should short-course therapy prove to be non-inferior, it may offer several advantages over standard-course therapy, including shorter hospital stays, reduced potential side effects from antibiotic treatment, lower costs, and a decreased likelihood of developing antibiotic resistance (1–6). However, if the non-inferiority of the trial treatment is not demonstrated, then the current standard treatment duration will be considered necessary and sufficient for this population.

This study will focus on several specific conditions. The antibiotic therapy duration may not affect outcomes in severe cases of AC (13). However, in the ICU, diseases such as septic shock can result in a mortality rate of approximately 20% (50). Therefore, patients admitted to the ICU or in an equivalent critical state will be excluded from the study. Retrospective studies have suggested that positive blood cultures and persistent fever do not affect outcomes (16,30,46,47). Consequently, we decided not to alter the duration of antibiotic therapy in cases where fever persisted, except in those with a high risk of infective endocarditis or *Staphylococcus aureus* detection, to maintain the same duration in cases with positive blood cultures (32,51). The applicability of standard or short-term treatment for patients with malignant tumor-induced multiple hilar biliary obstructions remains unclear. However, retrospective studies have reported frequent drainage inadequacies requiring repeated biliary drainage procedures in cases with multiple hilar biliary obstructions (20,52,53). These cases will be excluded because their investigation would require an evaluation of drainage methods, which is beyond the scope of assessing antibiotic therapy duration. Additionally, conditions such as pyogenic liver abscesses and acute cholecystitis are often observed simultaneously, necessitating different antibiotic treatment strategies for cholangitis. Therefore, cases with these comorbidities identified before registration will be excluded, while for patients who develop these conditions post-registration, the antibiotic therapy duration will be adjusted as appropriate for each condition (35–38).

The proposed trial has several inherent limitations. First, designing a double-blind trial was not feasible owing to practical considerations. Nevertheless, we believe that the defined outcomes are clear and will not be significantly compromised by the trial’s open-label design, as demonstrated in a similar previous study (13,35). Second, clinical outcomes will be assessed by attending physicians, which introduces an inherent risk of subjectivity in outcome assessment. However, the clear definitions of trial outcomes and the high cure rate of AC are expected to minimize this issue. Third, patients with multiple hilar biliary obstructions classified as Bismuth II or higher based on computed tomography and ERCP findings are considered susceptible to poor drainage and adverse prognosis and will be excluded. Therefore, a separate prospective study for this group will be necessary in the future.

Similar randomized controlled trials (RCTs) were conducted in India (13) and the Netherlands (COBRA trial, NCT05750966). An RCT conducted in India demonstrated the non-inferiority of a shorter antibiotic therapy duration within the range recommended by the TG18. In contrast, the treatment group in the COBRA study was quite aggressive, with an antimicrobial administration period of only 1 day, which does not allow the reflection of blood culture results. This trial is distinct from these two RCTs as it aims to examine a short-course therapy duration of 1–3 days for AC in Japan. Japan’s setting differs from that of India—known for its extremely high prevalence of resistant bacteria—and the Netherlands—known for its low prevalence (16,30,54–58). Currently, RCTs are independently conducted in different countries, but insights from multiple and diverse environments are beginning to emerge. We believe that this trial will contribute to advancing antibiotic stewardship by establishing a novel and optimized duration of antibiotic therapy for AC, thereby reducing the adverse events associated with antibiotic use, including increased antibiotic resistance.

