## Methods

### Design

We aim to conduct a multicenter, open-label, randomized trial to assess the non-inferiority of short-course therapy compared with standard-course therapy for AC management after successful biliary drainage. A comprehensive report of the trial will be prepared in accordance with the Consolidated Standards of Reporting Trials (CONSORT) guidelines, including specific recommendations for non-inferiority studies (17). This study was registered with the jRCT under the identifier jRCT1031230709. The protocol of this study was developed according to the Standard Protocol Items Recommendations for Interventional Trials (SPIRIT) guidelines, with the SPIRIT checklist included as Additional file. A detailed diagram of the methodology used in this study is shown in Fig. 1.

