### Randomization and allocation concealment

Participants in the study will be assigned to one of the treatment groups in a balanced 1:1 ratio within 24 h of the successful completion of biliary drainage. The allocation process will utilize a stochastic minimization method centrally managed by the study’s primary center at the Department of Gastroenterology, Shonan Kamakura General Hospital. A specialized electronic data capture system will be used for randomization and data collection. Stratification factors will include condition severity and facility as criteria.

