### Sample size

The clinical cure rates for short- and standard-course therapies were estimated using our retrospective dataset. According to a dataset of 361 patients that closely matched the control group in this trial, the clinical cure rate was 95.1% (135/142) in the short-course therapy group and 95.0% (208/219) in the standard-course therapy group, with an overall rate of 95.0% (343/361). This is consistent with the results reported in the literature (46,47). Therefore, a clinical cure rate of 95% was used in both groups for sample size calculation in this trial. The number of patients required for analysis was determined to be 200, with 100 cases per group, assuming a one-sided significance level of 2.5%, power of 90%, and a non-inferiority margin of 10% (39). Anticipating loss to follow-up and other contingencies, the target enrollment was set at 210, with 105 cases per group.

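### A failed non-inferiority test is pre-committed to mean that the standard duration is necessary and sufficient, which this two-arm design cannot show

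*Protocol article*

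**What the plan says.** The Design section describes a two-arm trial "to assess the non-inferiority of short-course therapy compared with standard-course therapy for AC management after successful biliary drainage". Randomization and allocation concealment gives 1:1 allocation. For the Sample size, "a clinical cure rate of 95% was used in both groups for sample size calculation in this trial", "assuming a one-sided significance level of 2.5%, power of 90%, and a non-inferiority margin of 10" percentage points. This gives 100 analysable patients per group, and "the target enrollment was set at 210, with 105 cases per group". The Statistical analysis section compares cure rates with 95% confidence intervals in the full analysis set and provides risk differences with 95% intervals. The interval method is not named.

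The Discussion then states what a negative result will mean: "if the non-inferiority of the trial treatment is not demonstrated", "then the current standard treatment duration will be considered necessary and sufficient for this population". The condition covers every failure of the test. Nothing elsewhere in the article separates an inconclusive result from evidence that the short course is worse.

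**The concern.** In a non-inferiority comparison, failure means that the lower confidence limit for short minus standard lies at or below −10 points. That limit can be reached with an interval that also covers zero and positive values.

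- *Necessary* would need evidence that the short course does worse. Failure to exclude a deficit is not such evidence.
- *Sufficient* would need the standard course to be compared with something else, such as a longer course or an absolute standard. The trial has no such arm or test.

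The stake is the conclusion of a trial whose stated purpose is antibiotic stewardship. An inconclusive result would be put forward as support for the longer course because of a sentence written before the data were seen.

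**Working it through.** **Inputs.** From Sample size: cure 95% in both arms, one-sided α 2.5%, power 90%, margin 10 points, 100 analysable and 105 enrolled per arm. From Statistical analysis: a 95% interval for the risk difference. Two assumptions are not in the protocol. One is the interval method, so Wald and Newcombe are both shown. The other is an alternative scenario of 93% on the short course against 95% on the standard course.

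**Step 1: reproduce the plan's figure.** With the unpooled normal approximation,

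n per arm = (z₀.₉₇₅ + z₀.₉₀)² × [p(1−p) + p(1−p)] / margin² = (1.960 + 1.282)² × (2 × 0.95 × 0.05) / 0.10² = 10.507 × 0.095 / 0.01 = 99.8, rounded up to 100.

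This matches the protocol. Approximate power at 100 per arm is 90.05%.

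**Step 2: one possible result.** Take 91/100 cured on the short course and 95/100 on the standard course. The difference is −4 points, with standard error √(0.91×0.09/100 + 0.95×0.05/100) = 0.0360. The Wald interval is −4 ± 1.96 × 3.60, or −11.1 to +3.1 points (Newcombe −11.8 to +3.5). Non-inferiority is not shown, yet the data are compatible with no difference and with a small advantage for the short course. The Discussion sentence would read this as the standard duration being necessary.

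**Step 3: how often this happens.** All pairs of cure counts were enumerated with their exact binomial probabilities, and each was classified by its two-sided 95% interval (L, U) for short minus standard. Failure is L ≤ −10 points. Failures divide into those with U ≥ 0 (inconclusive) and those with U < 0 (interval wholly below zero).

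| True cure, short vs standard | n per arm | Interval | All failures | Interval includes zero | Interval wholly below zero |
|---|---|---|---|---|---|
| 95% vs 95% | 100 | Wald | 11.4% | 8.9% | 2.5% |
| 95% vs 95% | 100 | Newcombe | 16.8% | 15.0% | 1.8% |
| 95% vs 95% | 105 | Wald | 10.0% | 7.4% | 2.6% |
| 95% vs 95% | 105 | Newcombe | 15.0% | 13.2% | 1.9% |
| 93% vs 95% | 100 | Wald | 33.5% | 24.6% | 9.0% |
| 93% vs 95% | 100 | Newcombe | 42.0% | 35.3% | 6.8% |

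(Components may differ from totals by 0.1 through rounding.)

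**Step 4: what the sentence adds.** Under equality the design itself accepts about 10% failure (1 − 0.90). That accounts for most of the 11.4–16.8%; the remainder comes from the interval method and the exact calculation. Of the failures at 100 per arm, 78% (Wald, 8.9/11.4) to 89% (Newcombe, 15.0/16.8) have an interval that includes zero. In those trials the data do not show the short course to be worse, but the sentence would still call the standard duration necessary.

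**The case against.** The strongest reply is that this is one sentence in the Discussion. It alters no endpoint, margin, significance level, population or test. It says *will be considered*, which can be read as meaning that current practice stays in place if the short course fails its test. The protocol also commits to reporting risk differences with 95% intervals and to the CONSORT recommendations for non-inferiority trials, so readers would see an interval that crosses both −10 and zero.

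Much of this stands, and it lowers the severity. It does not rescue the wording. Keeping current practice by default differs from concluding that it is necessary and sufficient, and a visible interval does not correct a conclusion that contradicts it.

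Three stronger readings are not supported:

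- A reader might infer that the plan treats failure as *proof*. The document does not go that far.
- A reader might take the whole 11–17% failure rate under equality as the size of the error. Most of it is type II error that the stated 90% power already discloses. It falls to about 10–15% at the enrolment target of 105 per arm, and it includes about 2% of trials whose interval lies wholly below zero. Likewise, not all of the 34–42% at 93% against 95% is misreading: the short course is truly 2 points worse there, and only 25–35% of trials fail with an interval that includes zero.
- A reader might infer a fault in the Sample size section. It reproduces, and it only supplies inputs here.

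**Conclusion.** The concern holds in limited form. As written, the sentence turns any failure to show non-inferiority into a finding of necessity, which such a failure cannot establish, and of sufficiency, which is never tested. The results that would be misread are those that fail with an interval including zero: about 9–15% of trials at 95% cure in both arms with 100 per arm, 7–13% with 105 per arm, and about 25–35% at 93% against 95% with 100 per arm. The ranges run from the Wald to the Newcombe interval because the article names no method, and they depend on the assumed cure rates. Should-fix: the conclusion drawn is affected; the test and its type I error are not.

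**What to change.** Delete the claim of necessity and sufficiency. Replace it with mutually exclusive readings of the two-sided 95% interval for short minus standard cure:

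1. Lower bound above −10 points: non-inferior. If the upper bound is also below 0, add that the short course is statistically worse but within the margin.
2. Lower bound at or below −10 points and upper bound below 0: short course worse. Describe it as inferior beyond the margin only if the upper bound is below −10 points.
3. Lower bound at or below −10 points and upper bound at or above 0: inconclusive. Report the interval and draw no conclusion that the standard duration is necessary.

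The added clause in reading 1 is needed because both conditions can hold at once. With 95/100 on the short course and 100/100 on the standard course, the Wald interval is −9.3 to −0.7 points. This is rare (about 0.2% of trials at 95% in both arms, Wald), but the rule should cover it.

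The cost is one sentence replaced by a short rule, with no effect on patients, data or sample size. It is best done before outcome data are analysed, since a change after a failed result would look post hoc.

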## Trial status

The protocol was initially on version 1.3 when patient recruitment began on June 1, 2024, and the first patient was recruited on June 5, 2024. During the recruitment phase, the protocol was updated to version 2.2, dated April 3, 2025. The trial is scheduled to end on March 31, 2027.

## Data Availability

The datasets used and/or analyzed in the current study are available from the corresponding author upon reasonable request.

## Abbreviations

AC: Acute cholangitis
TG18: Tokyo Guidelines 2018
IV: Intravenous
CONSORT: Consolidated Standards of Reporting Trials
SPIRIT: Standard Protocol Items Recommendations for Interventional Trials
ERCP: Endoscopic retrograde cholangiopancreatography
ICU: Intensive care unit
ULN: Upper limit of normal
CRP: C-reactive protein
WBC: White blood cell
HIV: Human immunodeficiency virus
SPILF: Société de Pathologie Infectieuse de Langue Française
SAE: Serious adverse events
RCT: Randomized control trial
NEWS: National Early Warning Score
ITT: Intention to treat
*C. difficile*: *Clostridioides difficile*
ALT: Alanine aminotransferase
ALP: Alkaline phosphatase
FAS: Full analysis set
PPS: Per protocol set
CRS JSRM: Clinical Research Support Unit of the Japanese Society for Regenerative Medicine
IRB: Institutional Review Board
